### Sample size

We powered this study on mental well-being outcomes, as measure by the HSCL [41], which reflected the most restrictive primary outcomes in terms of required sample size. Various studies from Ethiopia and East Africa suggest that approximately 20–35% of rural women experience elevated symptoms of common mental disorders such as anxiety and depression [44, 45]. Drawing on two studies that have used the HSCL in East Africa [41], we estimated that average scores generated by this tool would be around 1.5 (SD 0.5). Using unpublished data from a large on-going study of young people in Ethiopia [46], we estimated the intra-cluster correlation (ICC) for a measure of mental health was approximately 0.05, although we suspected this may be low given the sample consists of young people, and the measure captures more severe mental health symptoms. Unpublished data from rural households in South Omo, Ethiopia are approximately 33% higher on a common mental health scale; suggesting that water insecurity is linked to mental health, and the effect is appreciable [47]. There are limited data on the impact of changes in WASH on mental well-being, so we used a similar difference to estimate our impact. Our sample size determination (Additional file 3: Table S2) indicated that we should recruit and enroll a total of 25 households from each of 50 study clusters (25 clusters per study arm). We increased our final sample size to accommodate for 20% of households being lost to follow-up. Our target sample, therefore, included 30 households in each *kebele* study cluster, or 1500 households in total (i.e., 750 per study arm).

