Recruitment took place within the home compounds during baseline data collection. Enumerators contacted adult members of the household; they explained the purpose of the visit, the purpose of the study, and asked the respondent if s/he would be willing to consent to participate in the study using a structured consent form (Additional file 4). Enumerators assessed household level eligibility by asking potential survey respondents a series of questions that lead to a determination of eligibility, and enrolled eligible and consenting households into the trial. During the consent process, enumerators informed respondents that they had the right to choose not to participate in the study, the right to refuse to answer any question, and the right to stop the survey for any reason at any point in time. Enumerators targeted primary survey respondents, based on the following order of priority: (1) the primary female caregiver of the index child, (2) any female household member who serves as a caregiver, (3) any male household member who serves as a caregiver, and (4) any household member over 18 year of age. If households were absent after three visits, no eligible adult respondent was available or refused to consent, or upon further conversation with the household, it became apparent that it was not eligible (e.g., no child aged 1–9 years), the enumerator recorded the information and notified the field supervisor prior to replacing that household with the next randomly selected household on the study roster. Of 1691 surveys initiated during baseline, 1589 (94%) households met all inclusion criteria and were enrolled into the study – 89 households more than the targeted sample size. Targeted households that did not meet inclusion criteria were excluded for the following reasons: 81 households did not have a household member between 1 and 9 years of age, 17 households had no eligible respondent available, three surveys were initiated but not fully completed, and one household did not consent to participate.

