### Random allocation

Following baseline data collection, we used a stratified random design to assign study *kebeles* to either the *Andilaye* intervention or control arm (CLTSH). Within each stratum (*woreda*), researchers from Emory University in Atlanta, USA used a computer-based random number generator to generate a random number between zero and one for each *kebele* cluster, and then placed the clusters in ascending order by their randomly generated numbers. We then partitioned the communities within each *woreda* into two equal sizes, assigning the first half of *kebeles* to the intervention arm and the second half to the control arm. We used replacement re-randomization [51] to secure balance across three key variables (latrine coverage, washing station with soap coverage, and head of household education), as indicated by our baseline survey. CRTs, particularly trials with a small number of clusters, often have individual-level imbalances between study arms. Therefore, we established a priori that the intervention and control mean values for these three variables should be within two standard deviations of the overall mean for these variables. The randomization process described above was repeated (twice) until these variables were balanced according to that *a prior* criterion. Results from our equivalence analyses indicated balance in the number of previously triggered and ODF certified *kebeles*, between study arms, with 20 triggered and ODF *kebeles* in the intervention arm (80%, 20 of 25 study clusters) and 19 in the control arm (76%, 19 of 25 study clusters). Figure 3 provides further details in a flow diagram.

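### The 20% loss allowance was added as 25 × 1.2 = 30 households per kebele, which covers only 16.7% loss; covering 20% takes 25/0.8 = 31.25

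*Protocol article*

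**What the plan says.** All the figures needed stand in the protocol article.

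- **Requirement.** The Sample size section concludes that "we should recruit and enroll a total of 25 households from each of 50 study clusters (25 clusters per study arm"). That is 1,250 households, 625 per arm.
- **Allowance.** The next sentence reads: "We increased our final sample size to accommodate for 20% of households being lost to follow-up".
- **Target.** The result follows directly: "Our target sample, therefore, included 30 households in each" kebele, "or 1500 households in total (i.e., 750 per study arm").
- **Enrolment.** The Recruitment section reports 1,589 households enrolled, described as "89 households more than the targeted sample size".

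The text gives no other allowance and no rounding rule between the 25 and the 30. The derivation of the 25 is in Additional file 3, which is not shown.

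**The concern.** The 20% is stated as a share of households lost, so it has to be taken from the number enrolled. To have n households left after a proportion d is lost, one enrols n/(1 − d). Enrolling n(1 + d) always falls short, because the loss is then taken from the larger number. The published target therefore lacks the property stated for it.

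Two things follow for a reader. Someone who later sees 20% attrition would believe the design requirement had been kept by the 1,500 target alone, when it would not have been. And someone reading the Recruitment section would take all 89 households above target as spare, when most of them make good the gap in the allowance.

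**Working it through.** **Inputs.** Requirement m = 25 per kebele, k = 50 kebeles (25 per arm), loss d = 0.20 and target 30 per kebele (1,500), all from Sample size. Enrolled 1,589, from Recruitment; 793 intervention and 796 control, from Table 1.

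**1. Reproducing the stated target.** 25 × (1 + 0.20) = 30, and 1,250 × 1.20 = 1,500. Both match exactly, so the target is a 20% increase on the requirement.

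**2. What the target leaves after 20% loss.** 30 × 0.80 = 24 per kebele; 1,500 × 0.80 = 1,200. The shortfall is 1 household per kebele, or 50 in total (50/1,250 = 4%).

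**3. The loss that 30 per kebele does cover.** 1 − 25/30 = 16.7%.

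**4. The target that covers 20%.** 25/0.80 = 31.25 per kebele. In total 1,250/0.80 = 1,562.5, so 1,563. Rounding up to 32 in every kebele would give 1,600. The total of 1,563 is 63 above the stated 1,500 (63/1,500 = 4.2%).

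**5. Actual enrolment.**
- 1,589/50 = 31.78 per kebele on average.
- After 20% loss: 1,589 × 0.80 = 1,271, or 25.4 per kebele. By arm: 793 × 0.80/25 = 25.4 and 796 × 0.80/25 = 25.5.
- Largest overall loss that keeps 1,250: 1 − 1,250/1,589 = 21.3%.
- Of the 89 households above 1,500, 1,563 − 1,500 = 63 fill the gap in the allowance and 1,589 − 1,563 = 26 are beyond it.

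**6. Effect on power.** Assumptions: two-sided alpha of 0.05 (the article states none), and 80% power at m = 25 (the article states 80% only for the calculation made after baseline). The design effect is 1 + (m − 1) × ICC, and the effective number per arm is 25m divided by it.

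| ICC | m | Design effect | Effective n per arm | Power |
|---|---|---|---|---|
| 0.05 | 25 | 2.200 | 284.1 | 80.0% |
| 0.05 | 24 | 2.150 | 279.1 | 79.3% |
| 0.026 | 25 | 1.624 | 384.9 | 80.0% |
| 0.026 | 24 | 1.598 | 375.5 | 79.0% |

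The article gives 0.05 as the planning ICC ("we estimated the intra-cluster correlation (ICC) for a measure of mental health was approximately 0.05") and 0.026 as the value found at baseline. With the planning SD of 0.5 for the HSCL score and ICC 0.05, the difference detectable with 80% power is (1.96 + 0.84) × 0.5 × √(2/n). This is 0.1175 at n = 284.1 and 0.1186 at n = 279.1.

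**The case against.** **The 25 is worded as a number to enrol, not a number to analyse, and its derivation is not shown.** This carries little weight. An allowance added on top of 25 makes sense only if 25 is the number to be kept, and the point tests only the step from 25 to 30, for which every input is printed.

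**The error has no practical consequence.** This largely stands. Recruitment ended at baseline, the enrolled total covers a 20% loss on average, and the step from 25 to 24 costs about one power point or less, because the number of kebeles dominates precision in this design. What remains is a printed figure that does not do what the text says it does.

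**The Recruitment section is correct.** This stands. 1,589 − 1,500 = 89, and the sentence compares enrolment with the stated target.

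Three stronger readings are tempting, and the documents do not support them.

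- *Enrolment fell 11 short of a correct target of 1,600.* That total arises only if 31.25 is rounded up to 32 in all 50 kebeles; after 20% loss it leaves 1,280, which is 30 more than required. Against the 1,563 that the requirement implies, enrolment is 26 above.
- *None of the 89 is a surplus.* About 63 fill the gap in the allowance, and about 26 do not.
- *The 21% should serve as a minimum retention standard for every kebele.* It is an average. Enrolment per kebele is not given, so a kebele with fewer than 31.78 households could fall below 25 at a smaller loss. Nor is 25 a sharp threshold, given how little power changes at 24.

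**Conclusion.** The point holds as an arithmetic slip in the stated target. As written, 30 households per kebele accommodates 16.7% loss, not 20%; at 20% loss it leaves 24 per kebele and 1,200 in total, 4% below the requirement. This rests only on the article's own 25, 20% and 30, and takes the 25 as given.

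The point is minor. Under the assumptions stated in the working, power would be about 1 point lower or less. The 1,589 households enrolled restore the intended margin on average, with 26 to spare over 1,563, although single kebeles cannot be checked from what is shown. The slip does not make the trial underpowered.

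**What to change.** Correct the sentence in Sample size in one of two ways:

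- keep 30 per kebele (1,500) and say that it accommodates 16.7% loss to follow-up; or
- keep 20% and say that it requires 25/0.8 = 31.25 per kebele, about 1,563 in total (32 per kebele if rounded up in every cluster).

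With either, add that the 1,589 enrolled exceed 1,563 by about 26 households and, averaged over kebeles, tolerate about 21% loss, so that about 63 of the 89 households above the stated target make up the gap in the allowance.

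The cost is one or two sentences. The design, the enrolment and the analysis stay as they are.

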Following baseline, we conducted an ex-post power calculation on our main outcome. Given the prevalence of poor well-being (33.2% - Table 1), and a calculated ICC of 0.026, lower than expected, we determined that we were well powered (> 99%) to detect our original expected 37% relative reduction (an absolute difference of 12% points). Assuming 80% power, the absolute detectible difference is 8% points (a 24% relative reduction). For our other health outcomes, we conducted ex-post power calculations, and determined that we are able to detect a: 7%-point reduction in anxiety, with baseline of 29.7% (ICC: 0.007); 6%-point reduction in depression, with baseline of 20.8% (ICC: 0.01); and 5%-point reduction in emotional distress, with baseline of 17.3% (ICC: 0.005). Given the low prevalence of diarrhea (Table 1) and recent large-scale studies that showed mixed effects of the impact of WASH on diarrhea [48, 49], we considered this a secondary outcome. Given a baseline reported diarrheal prevalence of 9.1% for the index child during the past 7 days (ICC: 0.077), we are powered to see a 6%-point reduction in diarrhea outcomes.

**Table 1 Tab1:** Baseline data

Indicator	Overall		Intervention		Control	
Demographic information	N	%	N	%	N	%
Respondent was female	1589	90.7	793	91.3	796	90.1
Respondent was mother of index child	1589	84.6	793	85.4	796	83.9
Primary caregiver/mother has at least secondary education	1589	12.8	793	11.9	796	13.8
Primary caregiver/mother is married	1587	89.3	792	91.2	795	87.4
Head of household has at least some secondary education	1579	16.7	791	15.2	788	18.2
Demographic information	N	mean (SE)	N	mean (SE)	N	mean (SE)
Respondent’s age	1589	33.5 (0.38)	793	33.7 (0.52)	796	33.3 (0.55)
Head of household age	1589	41.3 (0.46)	793	41.6 (0.54)	796	41.1 (0.73)
Number of household members	1589	5.3 (0.08)	793	5.3 (0.10)	796	5.3 (0.12)
Household latrine coverage	N	%	N	%	N	%
Households with access to at least one household latrine	1589	65.5	793	64.1	796	66.8
Households with access to an improved household latrine ^a^	1553	39.8	775	39.9	778	39.7
Households with access to a fully constructed household latrine	1583	30.7	792	29.6	791	31.9
Household latrine operation and maintenance	N	%	N	%	N	%
Household has added or improved anything on the latrine since its original construction	1028	12.9	504	11.9	524	13.9
Household latrine characteristics	N	%	N	%	N	%
Presence of drop hole cover in the latrine	1033	13.4	505	12.5	528	14.2

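### Assuming a two-sided 5% test, 8 points on poor well-being has 69–71% power after the planned loss and 75–77% without loss, not the stated 80%; about 9 points is detectable after loss

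*Protocol article*

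**What the plan says.** All the power statements are in the protocol article, Methods, Sample size. The design calculation asks for "25 households from each of 50 study clusters (25 clusters per study arm"). The section then adds: "We increased our final sample size to accommodate for 20% of households being lost to follow-up". This gives 30 per kebele, "or 1500 households in total (i.e., 750 per study arm"). The Recruitment section reports 1589 households enrolled.

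The section then reports a second calculation: "Following baseline, we conducted an ex-post power calculation on our main outcome". Its inputs are introduced with "Given the prevalence of poor well-being (33.2% - Table 1), and a calculated ICC of 0.026, lower than expected". Two results follow for poor well-being. The authors say that "we were well powered (> 99%) to detect our original expected 37% relative reduction (an absolute difference of 12% points"), and that "Assuming 80% power, the absolute detectible difference is 8% points (a 24% relative reduction").

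For the other outcomes the section prints detectable reductions of 7 points (anxiety, baseline 29.7%, ICC 0.007), 6 points (depression, 20.8%, 0.01), 5 points (emotional distress, 17.3%, 0.005) and 6 points (7-day diarrhea, 9.1%, 0.077).

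The Analytical methods section plans linear regression for the mental well-being scale scores.

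**The concern.** The baseline prevalence, the ICC and the number of kebeles are all printed, so the 80% claim can be checked. It does not come out under a two-sided 5% test, and it moves further away once the planned loss is applied. The section enlarges the sample because a fifth of households may be lost, but does not say whether the later figures allow for that loss.

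Readers will use these figures to judge what a null result on the dichotomised outcomes can exclude. If 8 points is taken as the 80% difference, they will think a true 8-point reduction is missed 2 times in 10. With 25 households retained per kebele it is nearer 3 in 10.

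**Working it through.** **Inputs.** From Sample size: p1 = 0.332, ICC = 0.026, c = 25 kebeles per arm, m = 25 retained per kebele. From Recruitment: 1589/50 = 31.78 enrolled per kebele. Applying 20% loss gives 24 from the target of 30 and 25.4 from the number enrolled, so 25 is a fair value. *Assumption:* two-sided 5%; the article states neither alpha nor sidedness.

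**The plan's own percentages.** 8/33.2 = 24%, as printed. 37% of 33.2 is 12.3 points, printed as 12. These agree.

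**Design-effect formula.** n_eff = c·m / (1 + (m − 1)·ICC); power = Φ(d / √[(p1q1 + p2q2)/n_eff] − 1.96). For d = 0.08, p2 = 0.252 and p1q1 + p2q2 = 0.4103.

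- Full enrolled sample: design effect 1.800, n_eff 441, SE 0.0305, 0.08/SE = 2.624, power Φ(0.664) = 74.7%.
- 25 retained: design effect 1.624, n_eff 385, SE 0.0327, 0.08/SE = 2.450, power Φ(0.490) = 68.8%.
- n_eff needed for 80% power at 8 points: (1.960 + 0.842)² × 0.4103/0.08² ≈ 503 per arm, more than either.

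**Hayes-Moulton formula** (c clusters, the more favourable variant). k² = ICC(1 − p1)/p1 = 0.0523; V = (p1q1 + p2q2)/m + k²(p1² + p2²); power = Φ(√(c·d²/V) − 1.96).

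- Full enrolled sample: V = 0.0220, power Φ(2.697 − 1.960) = 76.9%.
- 25 retained: V = 0.0255, power Φ(2.505 − 1.960) = 70.7%.

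**12 points** (p2 = 0.212, design effect). Full sample: 0.12/0.0297 = 4.043, power 98.1%. 25 retained: 0.12/0.0318 = 3.775, power 96.5%.

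**All printed figures.** Differences are in points at 80% power.

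| Basis | Poor well-being | Anxiety | Depression | Distress | Diarrhea | Power at 12 / 12.3 points |
|---|---|---|---|---|---|---|
| Printed | 8 | 7 | 6 | 5 | 6 | > 99% |
| Two-sided, full sample, design effect | 8.52 | 6.80 | 6.12 | 5.32 | 6.10 | 98.1% / 98.6% |
| Two-sided, full sample, Hayes-Moulton | 8.29 | 6.74 | 6.04 | 5.28 | 5.82 | 98.8% / 99.1% |
| Two-sided, 25 retained, design effect | 9.09 | 7.48 | 6.67 | 5.86 | 6.28 | 96.5% / 97.2% |
| Two-sided, 25 retained, Hayes-Moulton | 8.88 | 7.43 | 6.60 | 5.83 | 6.03 | 97.4% / 97.9% |
| One-sided, 25 retained, design effect | 8.11 | 6.68 | 5.97 | 5.25 | 5.70 | 98.3% / 98.7% |

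**How much of the gap is loss?** By the design effect, power at 8 points falls from the stated 80% to 74.7% without loss and to 68.8% with it, so loss accounts for 5.9 of 11.2 points, about half. By Hayes-Moulton it accounts for 6.2 of 9.3, about two-thirds. The rest comes from formula and rounding.

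**The case against.** The strongest reply is that the printed figures are whole points and can be reproduced. Two-sided Hayes-Moulton on the full enrolled sample rounds to all five differences and gives 99.1% for the 37% reduction. That stands, so it would be wrong to say that no standard calculation leads to the printed numbers. However, it analyses every enrolled household, and an 8.3 rounded down to 8 still has 77% power, not 80%.

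A reader might infer that the figures fall short because loss was left out, and that every detectable difference ignores it. The article does not support this as fact. It does not give the cluster size used. A one-sided 5% calculation with 25 retained, so with loss included, also rounds to all five differences, although it gives 98.3–98.7% where the article prints over 99%. Power at 8 points is also below 80% in the two-sided calculation with no loss.

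A reader might also infer that the trial is underpowered, or that its mental well-being analysis would miss a real effect 3 times in 10. Neither follows. The 12-point target keeps at least 96% power. The scale scores are to be analysed as continuous outcomes, and these figures describe the dichotomised ones. The models also include woreda, which these formulas ignore. Finally, the calculation was made after enrolment, so no recruitment decision depended on it.

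**Conclusion.** The point holds as a stated power that the design does not deliver under a two-sided 5% test, particularly after the loss planned in the same section. The size depends on formula only within narrow limits: 69–71% power at 8 points with 25 retained, 75–77% with no loss, and a detectable difference after loss of 8.9–9.1 points. With 25 retained, the other four become about 7.4–7.5 (anxiety), 6.6–6.7 (depression), 5.8–5.9 (emotional distress) and 6.0–6.3 (diarrhea).

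The overstatement at 12 points is minor: 96–97% after loss and 98–99% without.

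These results rest on the assumed two-sided 5% level, equal cluster sizes and the printed ICCs. The documents do not settle why the printed figures differ.

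**What to change.** State the significance level, sidedness, formula and households per kebele behind the calculation. Recompute all five detectable differences and the 12-point power on that one basis, preferably two-sided 5% with 25 retained per kebele, and print the differences to one decimal. On that basis poor well-being becomes 8.9–9.1 points depending on the formula named, the other four fall in the ranges given above, and the over-99% figure becomes about 96–97%. If a one-sided test was used, say so and justify it.

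Add a sentence saying that these figures apply to the dichotomised outcomes and not to the linear regression of scale scores.

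The cost is a short recalculation and a few changed numbers, slightly less favourable than those printed. Design, sample and data collection are unaffected.

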Among those with a drop hole, a cover was situated over drop hole	138	66.7	63	65.1	75	68.0
Defecation practices	N	%	N	%	N	%
Respondent’s primary place of defecation was in the open during last 2 days	1589	37.5	793	39.5	796	35.6
Respondent defecated in any latrine during last 2 days	1589	45.6	793	46.0	796	45.1
Child feces were safely disposed of during the last 2 days	961	40.2	463	38.9	498	41.4
Sharing of household latrine facilities	N	mean (SE)	N	mean (SE)	N	mean (SE)
Given household has a household latrine, number of people from another household who used this latrine during last 7 days, exclusive of household members	1037	0.94 (0.12)	506	1.08 (0.18)	530	0.79 (0.14)
Animal husbandry / other household sanitation practices	N	%	N	%	N	%
Animal feces/waste not left out in open in compound	1589	44.1	793	42.0	796	46.2
Facial cleanliness among children aged 1–9 years	N	%	N	%	N	%
Ocular discharge present	1944	40.3	932	42.2	1012	38.6
Wet nasal discharge present	1944	47.3	932	47.6	1012	46.9
Dry nasal discharge present	1944	65.4	932	64.7	1012	66.1
Dirt/dust/other debris present	1944	69.9	932	68.7	1012	71.0
	N	mean (SE)	N	mean (SE)	N	mean (SE)
Number of times a fly land on the index child’s face during a 1 min observation	1382	4.2 (0.23)	669	4.1 (0.34)	713	4.3 (0.32)
Household washing station coverage	N	%	N	%	N	%
Household hand or facewashing station(s)	1589	78.9	793	77.1	796	78.8
Handwashing practices	N	%	N	%	N	%
The last time the respondent washed, s/he used soap/ash/soapy water	1588	36.4	793	35.1	795	37.7
The last time the respondent defecated, s/he cleaned hands with water and soap, substitute	1585	37.2	791	36.3	794	38.0
The last time the respondent prepared food, s/he cleaned hands with water and soap, substitute before beginning food preparations	1586	39.7	791	41.0	795	38.5
Diarrhea among index children	N	%	N	%	N	%
During the last 2 days, including today, index child had three or more loose stools per day	1577	6.3	782	5.6	795	6.9
During the last 7 days, including today, index child had three or more loose stools per day	1575	9.1	778	8.1	797	10.0
Anxiety and depression	N	% Mean (SD)	N	% Mean (SD)	N	% Mean (SD)
Anxiety ^b^	1584	29.7 1.56 (0.62)	790	29.6 1.56 (0.60)	794	29.7 1.56 (0.63)
Depression ^b^	1588	20.8 1.46 (0.52)	793	21.3 1.45 (0.51)	795	20.4 1.46 (0.52)
Emotional distress ^b^	1583	17.3 1.38 (0.48)	790	17.2 1.38 (0.47)	793	17.4 1.38 (0.48)
*WHO-5 well-being*	N	% Mean (SD)	N	% Mean (SD)	N	% Mean (SD)

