Poor well-being ^c^	1586	33.2 16.0 (7.0)	792	31.1 15.6 (7.1)	794	35.3 16.3 (6.8)

^a^ "Improved" based on the WHO/UNICEF Joint Monitoring Programme (JMP) for Water Supply and Sanitation definition. ^b^ We asked respondents to indicate how much the symptoms bothered them in the previous week with four potential response options (not at all [1] to extremely [4]). The first ten symptoms assess anxiety (i.e., ‘suddenly scared for no reason’, ‘nervousness or shakiness inside’), the next 13 assess depression (i.e., ‘feeling low in energy’, ‘feeling hopeless about the future’), and the 23 collectively assess non-specific emotional distress. For each outcome, the score is the sum of the responses divided by the number of items. Each of these scores was dichotomized, with scores greater than 1.75 indicating a positive status for any of the three outcomes. ^c^ We asked respondents about well-being, and responses ranged from ‘(0) At no time’ to (5) All of the time’. Scores were summed, and range from 0 to 25; the higher the score, the better the well-being. Each of these scores was dichotomized with scores below 13 indicating poor well-being

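### The baseline emotional-distress mean of 1.38 cannot arise under its stated 23-item scoring rule, which gives about 1.50, so the score and the figures derived from it need rechecking

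*Protocol article*

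**What the plan says.** In the protocol article, Study outcomes and measures makes mental well-being a primary outcome, measured by WHO-5 and HSCL scale scores. Footnote b to Table 1 (Sample size) gives the HSCL scoring. Items are answered from 1 to 4. "The first ten symptoms assess anxiety", the next 13 assess depression, and "the 23 collectively assess non-specific emotional distress. For each outcome, the score is the sum of the responses divided by the number of items". A score above 1.75 counts as positive on all three scales.

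Table 1 prints prevalence, mean and SD for all respondents as follows:
- anxiety: "29.7 1.56 (0.62"
- depression: "20.8 1.46 (0.52"
- emotional distress: "17.3 1.38 (0.48"

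By arm, emotional distress is "17.2 1.38 (0.47" (intervention) and "17.4 1.38 (0.48" (control).

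The ex-post power paragraph in Sample size uses this row for its claim of a "5%-point reduction in emotional distress, with baseline of 17.3% (ICC: 0.005". The 17.3% appears again under Balance of treatment arms at baseline.

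**The concern.** A mean taken over all 23 items is a weighted average of the means of its two subsets and cannot fall below the smaller one. Table 1 shows it below both, in every column. Either the score was not computed as footnote b says, or footnote b does not describe the score that was computed.

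The scale belongs to an HSCL primary outcome, and the survey is repeated at midline and endline. A scoring error in the code would therefore carry into the trial's results. It matters most for the binary version, because a fixed threshold applied to a deflated score counts too few respondents as positive. It would also leave emotional distress classified by a stricter effective threshold than anxiety and depression, although footnote b applies one threshold to all three.

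**Working it through.** **Inputs (Table 1 and footnote b).** Anxiety has 10 items, with mean 1.56 in every column. Depression has 13 items, with mean 1.46 overall, 1.45 intervention and 1.46 control. Emotional distress has 23 items, with printed mean 1.38 in every column. Respondents number 1584, 1588 and 1583 respectively.

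**1. The plan's own rule.** Emotional distress = (10 x anxiety mean + 13 x depression mean)/23.
- Overall: (15.60 + 18.98)/23 = 34.58/23 = 1.503
- Intervention: (15.60 + 18.85)/23 = 34.45/23 = 1.498
- Control: 34.58/23 = 1.503

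The printed 1.38 is not reproduced.

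**2. Can rounding or missing responses explain it?** Rounding of the two means allows 1.498 to 1.508 overall. For the differing Ns, take the lower rounding limit and suppose that everyone dropped from the emotional-distress row had the maximum score of 4. Overall, the anxiety mean becomes (1584 x 1.555 - 1 x 4)/1583 and the depression mean (1588 x 1.455 - 5 x 4)/1583. The weighted result is 1.493. The same worst case gives 1.487 in the intervention arm and 1.494 in the control arm. None comes near 1.38.

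**3. Can two further items explain it?** The minimum response is 1, so two extra items give at least (34.58 + 2)/25 = 1.463. They cannot.

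**4. Which divisor fits?** Dividing the 23-item sums by 25 gives 34.58/25 = 1.383, 34.45/25 = 1.378 and 1.383, all of which round to 1.38. The implied divisors, sum/1.38, are 25.06, 24.96 and 25.06.

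The SDs do not settle the question. The implied anxiety-depression correlation is [(D x 0.48)² - (10 x 0.62)² - (13 x 0.52)²]/(2 x 6.2 x 6.76). This is 0.45 for D = 23 and 0.71 for D = 25, and both are possible.

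**5. Consequence for the threshold if the divisor was 25.** A cut at 1.75 on sum/25 equals 1.75 x 25/23 = 1.90 on the 23-item mean. Respondents between 1.75 and 1.90 were then counted as negative. The SD on the stated scale would be 0.48 x 25/23 = 0.52.

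**6. Corrected prevalence.** This needs the individual data. For an indication only, three assumed shapes were fitted to mean 1.503 and SD 0.52. Their shares above 1.75 are 22.6% (gamma), 18.6% (lognormal) and 25.3% (beta), so roughly 19 to 25%. The shapes are approximate: for anxiety they give 26.0, 22.0 and 28.9% against the reported 29.7%.

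**7. Detectable difference.** Assumptions: two proportions, two-sided alpha 0.05, 80% power, 25 clusters per arm, m households per cluster, and effective n per arm = 25m/[1 + (m - 1) x ICC] with ICC 0.005 kept.

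| Baseline prevalence | m = 25 | m = 30 | m = 31.8 |
|---|---|---|---|
| 17.3% (printed) | 5.88 | 5.46 | 5.33 |
| 18.6% | 6.07 | 5.64 | 5.51 |
| 22.6% | 6.61 | 6.13 | 5.99 |
| 25.3% | 6.92 | 6.42 | 6.27 |

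At m = 30 or 31.8 the printed inputs reproduce the stated 5 points. Over the assumed range the difference rises by about 0.2 to 1.0 point.

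**The case against.** The case against making much of this is substantial, and most of it stands.

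- **The divisor is inferred.** The article never mentions 25 items or a divisor of 25. Two of the three columns share the same inputs, so the threefold match is weaker confirmation than it looks.
- **A reader might infer that the 17.3% and the 5-point figure are themselves wrong.** The article does not show this. The share above a threshold on a combined score can lie below both subscale shares, so 17.3% is possible in itself. It fails only if it was cut from the faulty score, which is what footnote b implies but does not prove. The 5 points follow correctly from the printed inputs.
- **A reader might also infer that an 8% shrinkage (23/25 = 0.92) weakens the planned score analysis.** Under Analytical methods, scale scores go into linear regression. A constant divisor rescales estimate and standard error alike, so the test statistic and p-value do not change. Only the size of the estimate in score units changes.
- **Emotional distress is not the headline outcome.** Sample size treats WHO-5 poor well-being as the main outcome for the ex-post calculation and places emotional distress among the other health outcomes. It was not a balance variable in the re-randomization, and its means and prevalences are similar in the two arms.

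None of this rescues the printed mean. It contradicts its own definition, and nothing else in the article resolves the contradiction.

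**Conclusion.** The emotional-distress mean of 1.38 is impossible under footnote b. The rule gives about 1.50 in each column, a gap of 0.12 or a quarter of the printed SD (0.12/0.48). That conclusion is arithmetic on the article's own figures and needs no assumption beyond the stated scoring.

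What follows from it is conditional. Division by 25 is the likely cause but is unconfirmed. If it is the cause and the prevalence was cut from the same score, the effective threshold was about 1.90. The 17.3%, its ICC of 0.005 and the 5-point detectable difference then belong to a mis-scored variable. A corrected prevalence of roughly 19 to 25% depends on assumed distribution shapes. The accompanying rise in the detectable difference, at most about one point, also assumes that the ICC stays at 0.005.

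The WHO-5 power statement, the anxiety and depression rows and, with a constant divisor, the p-value of the linear model are not affected. The practical risk is misclassification on the binary outcome at midline and endline if the same code is reused, which the article neither shows nor excludes.

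**What to change.** Check the scoring code for emotional distress. If it departs from footnote b, rescore as the sum of the 23 responses divided by 23 and reapply the stated 1.75 threshold. Then restate:
- the mean, SD and prevalence in the Table 1 row, overall and by arm;
- the baseline prevalence, ICC and detectable difference in the ex-post power paragraph of Sample size;
- the prevalence under Balance of treatment arms at baseline.

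Use the corrected code at midline and endline. If a different item set or denominator was intended, amend footnote b to describe it and say how the 1.75 threshold relates to it.

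The cost is one check of the scoring code, one table row and two sentences. No new data and no design change are needed.
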